### 2.5. Exclusion Criteria

Individuals with: (1) history of eczema/skin breakdown/other dermatological condition (e.g., psoriasis) affecting the skins behind the ears; (2) HIV/AIDS infection, as HIV will lead to vestibular neuropathy; (3) use of beta-blockers/antidepressants/any other medications that may affect the neurostimulation; (4) history of stroke/epilepsy/severe head injury/neurosurgery; (5) active migraine with aura; (6) significant communicative impairments; (7) metal implant in brain or pacemaker, implanted defibrillator, deep brain stimulator, vagal nerve stimulator, etc.; (8) undertook corticosteroid treatment within the last six weeks before the first TPS treatment; (9) pregnancy or breastfeeding women; (10) cognitive impairment including Dementia/Alzheimer’s disease, and mild cognitive impairment; (11) history of Bipolar affective disorder, psychosis or substance use disorders; (12) regular use of antihistamine medication in the last 6 months (because histamine receptors are present in the vestibular system); (13) history of malignancy in the past 12 months; (14) a diagnosis of myelofibrosis/myelodysplastic syndrome; (15) history of vestibular dysfunction or inner ear infections/diseases; and (16) previous use of any VeNS device will be excluded in this study.

### 2.6. Screening and Self-Administered Questionnaire

Participants will complete an online application form soliciting sociodemographic information (age, gender, educational background, marital status, monthly household income, living circumstances, employment status, psychiatric history and duration of having anxiety symptoms (in years/months), currently taking prescribed or over the counter anxiolytics (yes/no), family history of anxiety disorder (yes/no), and other psychiatric disorders, etc.) before filling in the screening tools (GAD-7 and Insomnia Severity Index). Participants have to indicate their written consent in the online application form before proceeding to the screening procedures.

### 2.7. Randomization, Allocation, Blinding and Masking

All consenting participants will be listed in alphabetical order according to their surnames and each participant will be assigned a unique identifier. An independent statistician will use a computer-generated list of random numbers (www.random.org) (accessed on 1 April 2022) to ensure concealment of randomization. Randomization will be conducted by an independent statistician off-site using a stochastic minimization program to balance gender, age, and GAD-7 scores of the participants. Block randomization with blocks of 10 (total: 7 blocks) will be used to allocate treatment groups. Participants from each block will be randomly assigned to the active VeNS groups or the sham VeNS groups in a 1:1 ratio. To avoid information flow, participants and research associates will be blinded to the group allocation to minimize potential contamination of the effects of VeNS or subject bias. The Principal Investigator will not be involved in data collection or pre- and post-VeNS measurements. Outcome measurements will be conducted by the research associates. Participants will be asked to guess the grouping (active VeNS vs. sham VeNS) when filling in the face-to-face post-test survey after finishing the 4-week interventions to determine the success of subject blinding [29].

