## Abstract

The prevalence of symptoms of anxiety is increasing, especially during the COVID-19 pandemic. A home use transdermal neurostimulation device might help to minimize the severity of anxiety disorder. To the best of our knowledge, there is no clinical trial using transdermal neurostimulation to treat individuals with symptoms of anxiety in Asia. This gives us the impetus to execute the first study which aims at evaluating the efficacy of Electrical Vestibular Stimulation (VeNS) on anxiety in Hong Kong. This study proposes a two-armed, double-blinded, randomized, sham-controlled trial including the active VeNS and sham VeNS group. Both groups will be measured at baseline (T1), immediately after the intervention (T2), and at the 1-month (T3) and 3-month follow-up (T4). A total of 66 community-dwelling adults aged 18 to 60 with anxiety symptoms will be recruited in this study. All subjects will be computer randomised into either the active VeNS group or the sham VeNS group in a 1:1 ratio. All subjects in each group will receive twenty 30 min VeNS sessions during weekdays, which will be completed in a 4-week period. Baseline measurements and post-VeNS evaluation of the psychological outcomes (i.e., anxiety, insomnia, and quality of life) will also be conducted on all participants. The 1-month and 3-month follow-up period will be used to assess the long-term sustainability of the VeNS intervention. For statistical analysis, ANOVA with repeated measures will be used to analyze data. Missing data were managed with multiple mutations. The level of significance will be set to *p* < 0.05. Results of this study will be used to determine whether this VeNS device can be considered as a self-help technological device to reduce perceived anxiety in the general population in the community setting. This clinical Trial was registered with the Clinical Trial government, identifier: NCT04999709.

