### 2.2. Subjects and Sample Size Estimation

Since the collaborative UK study is ongoing, we thus have to take reference of a similar CES study on GAD [23] on ‘Clinical effectiveness and cost minimization model of Alpha-Stim cranial electrotherapy stimulation in treatment seeking pts with moderate to severe GAD’. Participants in the CES group had a significant reduction in GAD-7 score (from baseline 15.77 (3.21) to 10.14 (4.86) (Cohen’s *d* = 1.3)) after 4 weeks of CES treatment.

Considering this trial is a sham-controlled trial, we hypothesize a large effect in the MS group. We used G*power version 3.1.9.7 (https://stats.oarc.ucla.edu/other/gpower/) (accessed on 1 April 2022) nto calculate the target sample size. With a statistical power of 99% and a statistical significance level at 0.05 to detect a large between-groups effect size of 1.3, each group will require 33 subjects. With an estimated attrition rate of 30% during the 12-week post-treatment follow-up, a total sample of 66 is required in this trial.

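### Section 2.7 names both stochastic minimisation and fixed blocks of 10 as the allocation method without saying which decides, and the analysis would usually leave the balancing factors unadjusted

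*Protocol article*

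**What the plan says.** All of the allocation text is in Section 2.7 of the protocol article. In order, it states:

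- a listing step: "All consenting participants will be listed in alphabetical order according to their surnames", with a unique identifier for each person;
- a computer-generated random-number list held by an independent statistician, said to serve concealment;
- randomisation by that statistician, off-site, "using a stochastic minimization program to balance gender, age, and GAD-7 scores of the participants";
- then: "Block randomization with blocks of 10 (total: 7 blocks) will be used to allocate treatment groups", with 1:1 assignment among the participants of each block.

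The total is fixed elsewhere. The Abstract says "A total of 66 community-dwelling adults aged 18 to 60 with anxiety symptoms will be recruited in this study", and Section 2.2 says "With an estimated attrition rate of 30% during the 12-week post-treatment follow-up, a total sample of 66 is required in this trial".

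Section 3 (Statistical Analyses) compares sociodemographic variables between arms by chi-square and t-tests and treats them as confounders only if they differ significantly. The primary analysis is a repeated-measures ANOVA of GAD-7 with group, time and their interaction. Baseline GAD-7 is compared by a t-test, and no consequence is attached to the result.

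**The concern.** Two consecutive statements each present a complete method for assigning the same participants. This is not operational detail left to a fuller document: the article names two mechanisms and leaves them unreconciled.

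Two things are at stake. First, two teams working from Section 2.7 could build different allocation systems, and an auditor could not say which of them complied. Each reading gives up something that the section promises: the covariate balance, or the 1:1 assignment within blocks of 10. Second, the analysis should reflect how people were allocated. When covariates are used to balance the arms and are related to the outcome, leaving them out of the model generally makes the standard error of the treatment effect too large. Section 3 decides on adjustment through significance tests at baseline, which is a poor guide under either scheme and especially under minimisation.

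**Working it through.** **1. The two mechanisms side by side.**

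| | Stochastic minimisation | Blocks of 10 at 1:1 |
|---|---|---|
| Next assignment depends on | gender, age and GAD-7 of those already allocated, plus a random element | position in a pre-generated sequence |
| Property secured | approximate balance on the three factors | 5 active and 5 sham in each full block |
| Property not secured | 5:5 in any given run of ten | balance on the three factors |

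Reading 1:1 within each block as 5:5 is the ordinary meaning of the text. Only one mechanism can determine a given assignment unless a combining rule is stated, and Section 2.7 states none.

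**2. What the adjustment rule does.** Section 3 tests at p < 0.05.

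- If blocks decide, a factor that randomisation has not balanced shows a significant difference by chance about 1 time in 20.
- If minimisation decides, gender and age are actively balanced, so the rule is triggered more rarely still.
- Baseline GAD-7 is not a sociodemographic variable, so on a literal reading the rule never covers it.

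The three balancing factors would therefore usually be missing from the model as covariates.

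**3. The sample size, reproduced.** Inputs from Section 2.2: "With a statistical power of 99% and a statistical significance level at 0.05" and "to detect a large between-groups effect size of 1.3, each group will require 33 subjects", with 30% attrition. Sidedness is not stated; two-sided is assumed here because it reproduces the stated figure.

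- Two-sample t-test, noncentrality d x sqrt(n/2), df = 2n - 2. At n = 23 per arm: 1.3 x sqrt(11.5) = 4.41, power 0.9906. This is the smallest n that reaches 0.99.
- Attrition: 23 / (1 - 0.30) = 32.9, rounded up to 33 per arm; 2 x 33 = 66.

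So 66 is the enrolment target with attrition already included, and no section gives a total of 70.

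**4. Seven blocks against 66 people.**

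- 7 x 10 = 70 places; 66 / 10 = 6.6, rounded up to 7. Seven is the smallest number of blocks of 10 that covers 66.
- Six full blocks give 30:30. The remaining 66 - 60 = 6 people take the first six places of a 5:5 block.
- P(k active among 6) = C(5,k) x C(5,6-k) / C(10,6), with C(10,6) = 210.

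| Split of last six | Final split | Probability |
|---|---|---|
| 3:3 | 33:33 | 100/210 = 0.476 |
| 4:2 either way | 34:32 | 2 x 50/210 = 0.476 |
| 5:1 either way | 35:31 | 2 x 5/210 = 0.048 |

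Power at d = 1.3 on all randomised is 0.9994 at both 33:33 and 31:35.

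**5. Chance imbalance in GAD-7 if blocks decide.** Taking the baseline SD of 3.21 from the CES study cited in Section 2.2 (an assumption for this population), the standard error of the difference in baseline means is 3.21 x sqrt(2/33) = 0.79 points. This is ordinary chance variation under any randomisation that does not balance on GAD-7. It shows what minimisation was meant to reduce, and it is not a bias.

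**The case against.** The strongest reply is that nothing here threatens validity. Assignment is by an independent off-site statistician, participants and research associates are blinded, and either method alone would be sound. That stands: it limits the risk that someone guesses late assignments in a block, and it means that no bias has been shown. It does not tell the reader which method is used.

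A second reply is that the two could be combined, for example by listing participants in batches of ten and choosing among 5:5 splits so as to balance the covariates. That would be workable, but the text does not say it.

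A third is that baseline GAD-7 already enters the repeated-measures ANOVA as a time point. This partly answers the concern for GAD-7. It does nothing for gender and age, and it is not the same as adjusting for baseline as a covariate.

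A reader might also infer stronger claims, which the document does not support:

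- *Four incompatible procedures.* The alphabetical list goes with the identifiers and assigns nobody. A random-number list can generate a blocked sequence or supply the random element of minimisation. The conflict is between two methods.
- *The randomisation cannot be carried out because 70 is not 66.* An incomplete last block is routine, and seven blocks are what 66 people need.
- *The alphabetical list conflicts with sequential recruitment.* Sequential allocation is not stated. Listing all consenters suggests that they are assembled first, in full or in batches, but the text does not settle it.

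**Conclusion.** The concern holds for the pair of methods. Section 2.7 gives stochastic minimisation and blocks of 10 as the allocation method for the same participants, with no rule of precedence or combination, so it does not define one procedure. The adjustment rule in Section 3 adds to this, because it would usually leave out the factors used to allocate.

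The size of the harm is modest. The block arithmetic is a clarification only: an exact 33:33 split is not guaranteed (probability 0.476), the worst case is 31:35, and power is unaffected to four decimals. The contradiction still needs to be resolved before anyone is allocated, because allocation underpins the randomised comparison and cannot be corrected afterwards.

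The conclusion on the contradiction rests on the wording alone. The figures assume 5:5 within full blocks, a two-sided test and, for the 0.79 points, the SD of the cited study.

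**What to change.** - State one scheme in Section 2.7 and delete the other. Either keep the planned minimisation on gender, age and GAD-7, say that it has a random element and how large that is, and drop the blocks; or keep concealed blocks and drop minimisation. If a combination is intended, write out the rule.
- Say whether allocation is sequential or in batches, and confine the alphabetical list and the random-number list to their actual roles.
- If blocks are kept, note that 66 leaves the seventh block incomplete, so that 33:33 is a target and not a guarantee.
- In Section 3, prespecify adjustment of the GAD-7 analysis for the factors used in allocation (gender, age and baseline GAD-7 if minimisation is kept), regardless of baseline significance tests.

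The cost is protocol wording and a small amount of analysis specification. The sample size does not change, and the minimisation program is already planned.

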### 2.8. Interventions

In this study, all participants (in both the active and sham VeNS groups) will receive a VeNS device for home use in our Integrative Health Clinic, School of Nursing, HKPU, after receiving the device training by the research associates. Participants will receive 20 VeNS sessions in total in this study, with each session lasting for 30 min over a 4-week period (i.e., Monday–Friday, total treatment time: 10 h). We believe that a four-week VeNS intervention will be sufficient enough to test the efficacy of VeNS on symptoms of anxiety. Participants will be followed up immediately after post-stimulation during the 4-week and 12-week periods (Figure 1, CONSORT Flow Diagram). We believe that a post-stimulation follow-up of up to 3 months is sufficient to evaluate the sustainability of VeNS.

#### 2.8.1. VeNS Group

Subjects should open the study app (VESTAL) prior to each VeNS stimulation session. Subjects will put on the VeNS headset (see Figure 2) and apply two self-adhesive electrode pads on the mastoid process behind the ear. Subjects should remain in a sitting down and resting position throughout the stimulation period. Subjects will then turn on the device which will then deliver a small electrical impulse (range from 0 mA to max. 1.5 mA, level 0–10) at 100 Hz. Subjects can adjust the device output until they are aware of a comfortable tingling sensation in the skin. The VeNS will then deliver the stimulation for 30 min and will automatically turn off. The level of stimulation is determined by a gentle swaying indicating modulation of the vestibular nerve. Subjects will be able to check their activities on the study app and modify the stimulation level either via the mobile app or via the iPods. The device can be paused/stopped by pressing the power button twice on the headset or via the study app. Subjects will hear a single beep sound whenever they change the stimulation level. After the stimulation, subjects can remove the headset and dispose the electrode pads.

#### 2.8.2. Sham VeNS

Subjects in the sham-controlled group will follow the identical procedures as set in the VeNS group. Subjects will receive the initial stimulation for 30 s and then tap down to 0 mA for 20 s. Each session will deliver a sham VeNS stimulation at a frequency of 0.8 Hz to reduce the likelihood of a vestibular sympathetic response that may induce weight loss [30]. Subjects will also experience sensations of skin tingling and vestibular stimulation so that subjects in this group will believe that they have been allocated with an active device.

On completion of each VeNS session, subjects will charge the device using the micro-USB and charger provided by the Project team for usage in the next stimulation session. The device will automatically stop the stimulation after 30 min of usage per day and subjects will need to undergo a 16-hour lock-out period to reuse the device again.

Data will be collected via the Bluetooth of the device. Total usage per day, average intensity used, and average resistance will be logged and stored on an encrypted server. The study app will automatically upload the data usage to our backend server when connected to Wi-Fi. All individual data with a unique trial identifier will be allocated at the recruitment time and collected via REDCAP by the PI and recorded in the electronic CRF.

### 2.9. Adverse Events and Safety Checklist

Given the low current (max. 1.5 mA) and voltage (4.25 v) of the Modius Stress device, it is generally safe for home users. However, some subjects may have skin irritation at the electrodes’ sites, sensation of disequilibrium, nausea/vomiting, headache, and an electrical tangling sensation. Hence, an adverse events checklist will be used to monitor/quantify the occurrence of these events in this trial. Subjects are encouraged to contact the project team members should these adverse effects become serious which warrant medical attention. The PI will then assess the subjects’ physical and mental conditions and decide whether they could continue the intervention or not.

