Since the 20th century, some promising research has demonstrated that VeNS can improve postural stability in patients with Parkinson’s disease [12,13,14], bilateral vestibulopathy [15], or patients of the elderly population [16,17]. Recent VeNS research also showed that repetitive stimulation of the vestibular system may influence hypothalamic control of metabolic homeostasis, and thus decrease fat storage. In other words, VeNS may well be considered as an alternate self-help treatment option for obesity, diabetes, or other related metabolic diseases [18]. Recent findings from meta-analysis also found that there was a positive association between diabetes and anxiety symptoms [19]. Such findings were also echoed by a recent metanalytic review that non-invasive brain stimulation had a significant effect on the reduction of anxiety symptoms [20]. Nonetheless, there seems to be no empirical evidence on the efficacy of VeNS on symptoms of anxiety in Asia, particularly in Hong Kong or China. This research gap has given us the impetus to execute this trial.

Vestibular Neurostimulation (VeNS)—Modius Stress (MS)

Modius Stress (MS) is a non-invasive, transdermal neurostimulation device with a battery-powered headset designed to transcutaneously deliver low-level electrical energy (0–1500 microamperes) to the subject’s head (neurostimulation) to treat anxiety. This MS delivers neurostimulation through two self-adhesive electrode pads which will be placed on the subject’s skin, overlying each mastoid process behind the ear. MS delivers a small electrical impulse which can be adjusted up or down by the subject using the buttons on the headset (max. 1.5 mA at 100 Hz) or via Bluetooth using the mobile app to a level (0–10) where the subject can feel the tingling sensation in the skin (Table 1).

The subject will determine the level of neurostimulation once they begin to experience the gentle swaying, indicating modulation of the vestibular nerve. This device will automatically turn off after 30 min of neuromodulation. The MS device will deliver a small electrical current onto the skin through the electrode pads. This electrical current serves as a neurosignaling waveform which modulates cranial nerves that influence the balance between the parasympathetic and sympathetic nervous systems. MS stimulates the head and vestibular nerves via Cranial Electrotherapy Stimulation (CES).

Cranial Electrotherapy Stimulation (CES) and past research using CES on anxiety

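### Section 2.9 counts as adverse events the tingling, and plausibly the balance sensation, by which participants are meant to set the stimulation level

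*Protocol article*

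**What the plan says.** Section 2.9 names five effects that some participants may have: skin irritation where the electrodes sit, then "sensation of disequilibrium, nausea/vomiting, headache, and an electrical tangling sensation". It continues: "Hence, an adverse events checklist will be used to monitor/quantify the occurrence of these events in this trial". The same section goes on to call them adverse effects. Its only graded wording asks participants to contact the team when an effect becomes serious, after which the principal investigator decides on continuation.

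The instructions for use give two of these sensations another role. Section 2.8.1 says: "Subjects can adjust the device output until they are aware of a comfortable tingling sensation in the skin". It adds: "The level of stimulation is determined by a gentle swaying indicating modulation of the vestibular nerve". The Introduction agrees on the second sign: "The subject will determine the level of neurostimulation once they begin to experience the gentle swaying, indicating modulation of the vestibular nerve". Section 2.8.2 has the sham arm follow the same procedures and says: "Subjects will also experience sensations of skin tingling and vestibular stimulation". The stated purpose there is that sham participants should believe their device is active.

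**The concern.** A sensation that marks a properly set device also appears on the list of harms, and the article states no rule that tells the two apart. A participant who uses the device as described has a reason to report tingling, and perhaps unsteadiness, at every session. Someone whose imbalance continues after the device has switched off could be recorded under the same item.

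What is at stake is how the tolerability data read. The article calls the device generally safe at home and hopes to support it as a self-help option. For a vestibular stimulator, lasting imbalance is a harm that one would want to see separately from the expected effect of a session. The primary outcome, GAD-7, is not affected.

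**Working it through.** The plan states no adverse-event rate and no adverse-event analysis, so there is no figure to reproduce. The check sets the sections side by side.

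| Item in section 2.9 | Used to set the level (Introduction, 2.8.1)? | Intended in sham (2.8.2)? | Overlap |
|---|---|---|---|
| Electrical *tangling* sensation | Yes, if read as tingling | Yes | Firm |
| Sensation of disequilibrium | Gentle swaying is used; related but not equated | Vestibular sensation, yes | Plausible |
| Skin irritation | No | No | None |
| Nausea/vomiting | No | No | None |
| Headache | No | No | None |

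Two of five items are therefore affected. The most active-arm sessions in which an intended sensation could be reported is 33 participants × 20 sessions = 660. That is a ceiling: it assumes full attendance and a report every time.

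**Effect on a pooled rate (illustration on assumed rates).** Let *h* be the proportion of an arm with a real harm and *s* the proportion who tick an intended sensation, independently of harm. Then

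P(any event) = 1 − (1 − *h*)(1 − *s*).

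With the same *s* in both arms, the between-arm difference is (*h* active − *h* sham)(1 − *s*). Taking *h* = 30% active and 10% sham:

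| *s*, both arms | Active | Sham | Difference (points) |
|---|---|---|---|
| 0% | 30.0% | 10.0% | 20 |
| 50% | 65.0% | 55.0% | 10 |
| 80% | 86.0% | 82.0% | 4 |
| 95% | 96.5% | 95.5% | 1 |

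If the arms tick at different rates, a difference appears without any difference in harm. With *h* = 10% in both arms, *s* = 80% active and 50% sham, the pooled rates are 1 − 0.9 × 0.2 = 82% and 1 − 0.9 × 0.5 = 55%. The 27-point gap arises only from who felt the intended sensation.

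The distortion can therefore go either way, depending on how far sham reproduces the sensations. The article says that it should reproduce them, but gives no rate.

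**The case against.** The strongest reply is that the checklist is not shown. Its form may grade severity and record timing, and a condensed article may leave those fields to the full protocol or case report form. This stands as a limit: nobody can say from the article that the data will be inseparable, or that every participant will tick the same box. It does not remove the point, because the article itself puts tingling both among the signs for setting the level and among the adverse effects whose occurrence is counted. That is a conflict in what is stated.

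Other parts of the reply also stand:

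- Gentle swaying is never equated with disequilibrium, and the qualifiers *gentle* and *comfortable* suggest some intended distinction. The overlap is firm only for tingling.
- A reader might infer that participants are told to turn the device up until they feel these effects. Section 2.8.1 says only that they can adjust the output, and the Introduction allows adjustment in both directions.
- A reader might infer that all adverse-event rates are uninterpretable. Three of the five items are not setting signs, and their separate counts are sound.
- A reader might infer that a planned between-arm safety comparison is spoiled. Section 3 plans no such comparison, and adverse events are not a listed outcome.
- Serious effects have their own route to the team and the investigator. That route handles escalation and does not decide what is counted, but it means that a serious harm need not surface only on the checklist.

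The sham arm gives some comparison, though a weak one for these two items, since it is designed to evoke similar sensations.

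**Conclusion.** The point holds in a limited form. As the article is worded, the tingling count, plausibly the disequilibrium count, and any pooled any-event rate mix the intended sensation with harm. Item-level skin irritation, nausea/vomiting and headache are unaffected.

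The conclusion assumes that *tangling* is a misprint for tingling and, for the second item, that participants could report swaying as disequilibrium. The documents do not allow an estimate of the distortion; the calculated differences rest on assumed rates and on independence of harm and intended sensation. Claims that the rates cannot separate harm from correct use, or that a real harm will be hidden, go further than the text allows while the checklist is unseen. This is a minor correction to safety recording, worth making because it is nearly free.

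**What to change.** Reconcile the Introduction and sections 2.8.1, 2.8.2 and 2.9 so that the text says when tingling or a balance sensation is recorded as an adverse event and when it is an expected effect of use. In the checklist:

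1. Record in-session tingling and gentle swaying at the chosen level on a separate expected-sensation line.
2. For any tingling or imbalance, record whether it was confined to the session or persisted after automatic switch-off, and whether it was distressing.
3. Report expected sensations and adverse events separately by arm, and keep expected sensations out of any pooled adverse-event rate.
4. Correct *tangling* if tingling is meant.

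A change of level should not by itself mark an event as adverse. The Introduction treats adjustment up or down as ordinary use, so that marker would bring back the same mixture.

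The cost is one or two extra checklist lines and a sentence in section 2.9. Sample size, visit schedule and primary analysis do not change.
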